### Process outcomes

As part of the intervention delivery, we will explore process outcome measures, such as the proportion of patients who automatically received the pre-visit medication list, the proportion of patients who used the intervention materials at home, and whether the intervention materials prompted physician-patient discussion.

### Study outcomes

This study is designed to target four key medication-related outcomes: medication reconciliation, medication understanding, regimen consolidation, and medication adherence.

#### Medication reconciliation

Numerous studies have shown discrepancies between the medications that patients report taking and those listed in their medical chart, undermining the quality and safety of clinical care [13-16]. The pre-visit medication list is designed to prompt greater physician-patient communication about medication use and to ensure that self-reported medication use matches the medications listed in the patient’s chart. To measure medication reconciliation, we will ask patients, during the one-month follow-up interview, what medications they are taking. We will compare self-reports with the medications listed in their chart. Research assistants will note any discrepancies and ask patients whether they are taking any medications that were not named but are listed in their charts. Similarly, the research assistant will inquire after any medications that the patient reports taking but are not on their medication list. This outcome will then be coded as: (1) no discrepancies present between self-report and medical chart or (2) discrepancies present. The number of and type of discrepancies will also be recorded and forwarded to supervising physicians in the research team for review, with clinically significant discrepancies being communicated to the patient’s primary care doctor immediately. This coding schema is consistent with previous studies on medication reconciliation [14,15].

#### Medication understanding

Numerous studies have found limited literacy skills and limited English proficiency to be associated with poorer recall of medication names and indications, inadequate understanding of prescription instructions and precautions, and poorly demonstrated use of medications and devices [11,17]. To measure patients’ understanding of their medication regimens, research assistants will guide each patient through a pill-dosing demonstration. Specifically, patients will be given a tray with 24 compartments, each representing one hour of the day. Patients will be oriented to the tray and then asked to show how they take each of their medications over a 24 hour period of time, using the tray and colored beads that represent pills. Research assistants will record when patients indicate that they take their medications, including dose, frequency, and spacing between doses; this will be coded as correct or incorrect, based on pre-established coding criteria [18].

#### Regimen consolidation

As part of this dosing exercise, we will also measure patients’ consolidation of their medication regimen. Research indicates an inverse relationship between dosing frequency and adherence [19-21]. Despite this, a recent study by our team demonstrated that many patients unnecessarily overcomplicate medication use by not consolidating a complex regimen so that it can be taken the minimum number of times per day [5]. Using the data from the dosing exercise, we will measure regimen consolidation, defined as the number of times per day when medication is taken, as indicated in the dosing exercise.

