### Analyses

A sample size of 600 patients, 300 in each arm, was determined for this research study based on sample size calculations for the outcome measure of medication understanding. Assuming an overall baseline rate of understanding of 65%, a sample of 300 patients per arm would enable the detection of an 11% absolute increase in medication understanding with 80% power. These differences were considered appropriate, based on the results of prior studies conducted by this study team [17,28,29]. This sample size also supports our exploratory analyses for the effects of the intervention on surrogate clinical outcomes. For example, a sample size of 600 provides adequate power (86%) to detect a difference of 3 mm Hg in mean systolic blood pressure by study arm, assuming a standard deviation of 12.

We will perform intent-to-treat analyses to determine the study results. Before conducting formal analyses, we will perform descriptive statistics to ensure adequate balance of patient characteristics across the two treatment arms (usual care and intervention) at baseline; *t* tests and *χ*^2^ tests will be used to evaluate differences across the two arms for continuous and binary variables, respectively. Generalized linear models will be used for data analyses using PROC GENMOD in SAS (version 9.2), specifying the logit link function for binary outcomes (medication understanding, reconciliation, adherence, and regimen consolidation) and the identity link function for continuous outcomes (blood pressure, hemoglobin A_1_c). The treatment group will be the independent variable of primary interest and will be modeled with usual care specified as the reference group. Any potential confounding covariates noted in the descriptive analysis will also be included in the models.

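### Regimen consolidation is a bare count of dosing times with no link to the prescribed regimen, so some omitted doses lower it, and the count does not match the binary analysis planned for it

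*Protocol article*

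**What the plan says.** Regimen consolidation is one of the four key outcomes under Study outcomes and part of the third specific aim.

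- **Concept.** The Regimen consolidation section says patients overcomplicate their medication use "by not consolidating a complex regimen so that it can be taken the minimum number of times per day". It adds the reason fewer times are preferred: "Research indicates an inverse relationship between dosing frequency and adherence".
- **Measure.** The same section then states: "we will measure regimen consolidation, defined as the number of times per day when medication is taken".
- **Source data.** Under Medication understanding, patients are "asked to show how they take each of their medications over a 24 hour period of time", with beads in a 24-compartment tray. Dose, frequency and spacing are recorded, and "this will be coded as correct or incorrect, based on pre-established coding criteria". That coding serves the understanding outcome.
- **Analysis.** The Analyses section has generalized linear models "specifying the logit link function for binary outcomes (medication understanding, reconciliation, adherence, and regimen consolidation", with the identity link kept for the continuous clinical measures.

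**The concern.** The concept compares what the patient does with the least the regimen needs. The measure records only what the patient does. A low count can therefore mean efficient grouping of doses or missing doses, and the definition cannot tell them apart.

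This matters for the comparison of arms because the intervention is meant to do both things. Methods/Design says the study seeks to reduce the confusion behind unintended missed doses and dosing mistakes; success there puts beads back in the tray. The post-visit list is meant to help patients organise their medicines into fewer, explicit times; success there takes dosing times away. Both effects arise after assignment, so randomisation does not separate them. The first interview follows the index visit, so the described schedule gives no count from before the intervention to adjust for.

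Separately, a count is not a binary variable. The article does not say how one becomes the other, so what a favourable result would mean is not fixed.

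**Working it through.** **Plan's own figures.** None concerns consolidation. The sample size rests on medication understanding, and it reproduces: with 65% read as the overall rate (59.5% against 70.5%), 300 per arm and two-sided 5% (assumed), power is 80.8% against the stated 80%. The present point does not touch it.

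**Step 1: what an omission does to the count.** The count is the number of distinct tray hours holding at least one bead. Removing a bead can never add an hour. It removes one exactly when that bead was alone at its hour.

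**Step 2: worked patterns.** Assume drugs X and Y twice daily and Z once daily, so the required minimum is 2 times.

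| Pattern shown | Hours used | Count | Count minus 2 | At or below 2? | Equal to 2? | All doses shown and at most 2 times? |
|---|---|---|---|---|---|---|
| Correct and grouped | 8, 20 | 2 | 0 | yes | yes | yes |
| Both evening doses omitted | 8 | 1 | −1 | yes | no | no |
| X evening omitted, Y evening kept | 8, 20 | 2 | 0 | yes | yes | no |
| Correct but scattered | 8, 10, 13, 20, 22 | 5 | 3 | no | no | no |
| Scattered, X evening omitted | 8, 10, 13, 22 | 4 | 2 | no | no | no |

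The raw count ranks the second patient ahead of the first, and the fifth ahead of the fourth. Subtracting the minimum keeps both rankings (−1 against 0, 2 against 3), because the minimum is the same whether or not a dose is shown. A cut at or below the minimum credits the second and third patients. A cut at exactly the minimum still credits the third. Only the last column gives no credit for an omission.

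**Step 3: illustrative size, all inputs assumed.** Simulated patients have three once-daily and two twice-daily drugs, half of the drugs taken at their own hour, and second doses omitted at random.

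| Second doses omitted | Mean count | Count 4 or fewer | Count 2 or fewer | Count exactly 2 |
|---|---|---|---|---|
| 0% | 4.39 | 51% | 5.2% | 5.2% |
| 10% | 4.26 | 57% | 5.8% | 5.8% |
| 20% | 4.12 | 62% | 7.1% | 6.9% |
| 30% | 3.98 | 68% | 8.9% | 8.3% |

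More omission looks better on every column. Going from 20% to 0% moves the mean by 4.39 − 4.12 = +0.27. Under the rule in the last column of step 2, the share consolidated is 5.2% × (1 − omission rate)², since both second doses must be shown: 5.2%, 4.2%, 3.3% and 2.5%. The direction is now right.

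**Step 4: offset on the count scale.** Let g be the true fall in mean dosing times from grouping, and d the rise from restored stand-alone doses. The observed difference is −g + d. The nearest planning figure is the 11-point gain in understanding. If none of the newly correct patients regains a stand-alone time, d = 0; if each regains exactly one, d = 0.11 × 1 = 0.11. With an assumed g of 0.20, the observed difference runs from −0.20 to −0.20 + 0.11 = −0.09. With g = 0.10 it runs from −0.10 to +0.01. Neither end is an estimate.

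**The case against.** The best defence is that the raw count may never be analysed. The Analyses section calls the outcome binary, an article commonly leaves a coding rule to the full protocol, and that rule could use the required minimum. That the rule may exist elsewhere stands, and so does the fact that fewer-is-better is inferred from the rationale rather than stated. But the article does state a definition, and it is a count without the minimum. Step 2 also shows that bringing in the minimum is not enough unless omitted doses are dealt with.

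Omission is also captured elsewhere: understanding codes it as incorrect, and adherence is measured in three ways. True, and this confines the damage, but it does not correct the consolidation score.

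Several stronger readings are tempting and are not supported:

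- *Every missed dose improves the score.* It does not. If another drug shares the hour the count is unchanged, and every participant takes at least three daily medicines, so sharing is plausible.
- *A working intervention will look null or harmful.* Offset is possible; its extent depends on omission rates the article does not give, and on a mean-count comparison it does not plan.
- *Differences between patients in required dosing times bias the comparison.* Patients are individually randomised, so differences present beforehand mainly cost precision.
- *The trial's main result is at risk.* The sample size rests on understanding, which does not use this count.

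**Conclusion.** The point holds as a defect in the definition of one of four key outcomes. The stated measure does not express the stated concept, it rewards omission of a required dose that stood alone at its hour, and its scale conflicts with the planned logit model. That omission can only lower the count or leave it unchanged follows by logic from the definition. That a lower count is favourable is inferred from the section's rationale. The size is unknown; the figures above show direction under assumed regimens and rates only. It should be put right before the outcome is analysed, but it does not affect power or the other three outcomes.

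**What to change.** Reconcile the Regimen consolidation and Analyses sections with one binary definition against each patient's own regimen:

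- **Consolidated:** all prescribed doses are shown in the tray, in no more than the minimum number of times the charted regimen requires.
- **Not consolidated:** everything else, including any patient who omits a required dose.

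Keep all randomised patients in the analysis. Restricting it to those who dose correctly would select on something the intervention may change and would depart from the intent-to-treat principle. Report the raw count and the excess over the minimum as supportive only, since neither removes the omission effect.

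The tray record and chart list already collected supply the data, and the result fits the planned logit model. The costs are a written rule for computing the minimum from the charted regimen, and partial overlap with medication understanding, because a patient who omits a dose now fails on both. That overlap should be acknowledged when the outcomes are read together.

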#### Medication adherence

Non-adherence to prescribed medications is well documented, highly prevalent, and common among patients with chronic conditions, with nearly half of patients taking less than 80% of their prescribed doses [3,22-24]. For this study, where data on adherence to multiple medications is collected, using technology such as medication event monitoring systems is not feasible. We are therefore following other adherence measurement guidelines and triangulating multiple measures of adherence [25]. Medication adherence will be assessed using the Morisky general measure of adherence, a directly observed pill count, and a 4-day self-reported assessment of pills missed [26].

### Key covariates

We will collect data on a number of key covariates, including age, sex, English proficiency, comorbidities, medication and healthcare utilization, income, and race and ethnicity. Health literacy will be measured using the Newest Vital Sign [27].

### Analyses

A sample size of 600 patients, 300 in each arm, was determined for this research study based on sample size calculations for the outcome measure of medication understanding. Assuming an overall baseline rate of understanding of 65%, a sample of 300 patients per arm would enable the detection of an 11% absolute increase in medication understanding with 80% power. These differences were considered appropriate, based on the results of prior studies conducted by this study team [17,28,29]. This sample size also supports our exploratory analyses for the effects of the intervention on surrogate clinical outcomes. For example, a sample size of 600 provides adequate power (86%) to detect a difference of 3 mm Hg in mean systolic blood pressure by study arm, assuming a standard deviation of 12.

We will perform intent-to-treat analyses to determine the study results. Before conducting formal analyses, we will perform descriptive statistics to ensure adequate balance of patient characteristics across the two treatment arms (usual care and intervention) at baseline; *t* tests and *χ*^2^ tests will be used to evaluate differences across the two arms for continuous and binary variables, respectively. Generalized linear models will be used for data analyses using PROC GENMOD in SAS (version 9.2), specifying the logit link function for binary outcomes (medication understanding, reconciliation, adherence, and regimen consolidation) and the identity link function for continuous outcomes (blood pressure, hemoglobin A_1_c). The treatment group will be the independent variable of primary interest and will be modeled with usual care specified as the reference group. Any potential confounding covariates noted in the descriptive analysis will also be included in the models.

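### Regimen consolidation is defined as a count of daily dosing times but assigned to the logit model for binary outcomes, with no rule for dichotomising it

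*Protocol article*

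**What the plan says.** Under Study outcomes, the protocol article names regimen consolidation as one of four targeted outcomes. Its own section measures it from the pill-tray exercise: "defined as the number of times per day when medication is taken, as indicated in the dosing exercise". That is a whole-number count, and lower means better consolidated.

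The Analyses section sets the models by outcome type. Regimen consolidation falls in the first group: "specifying the logit link function for binary outcomes (medication understanding, reconciliation, adherence, and regimen consolidation". The second group is "the identity link function for continuous outcomes (blood pressure, hemoglobin A_1_c", and regimen consolidation is not in it.

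The only wording that hints at two categories is the remark that an earlier study found many patients "not consolidating a complex regimen so that it can be taken the minimum number of times per day". It is offered as background, and the definition that follows does not use it.

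**The concern.** A binary logit model needs a yes/no response. Values such as 2, 3 or 4 dosing times cannot enter it until someone decides what counts as consolidated, and the article gives no such rule. Two analysts working from this text could therefore analyse different outcomes: the count, the count split at some number, or success judged against the fewest dosing times the patient's regimen allows. These are different estimands (a mean difference or rate ratio against an odds ratio) and can differ in power. If the rule were still open once data were visible, the choice could also be steered by the result.

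**Working it through.** **1. Definition against model for the outcomes on the logit list**

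| Outcome | How its own section codes it | Model in Analyses | Fit |
|---|---|---|---|
| Understanding | "this will be coded as correct or incorrect, based on pre-established coding criteria" | logit | yes |
| Reconciliation | "This outcome will then be coded as: (1) no discrepancies present between self-report and medical chart or (2) discrepancies present" | logit | yes |
| Regimen consolidation | a count, no categories | logit | no |
| Adherence | three instruments, scoring not given | logit | cannot be judged |

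Where the article means a binary outcome, it can state the two categories. For regimen consolidation it states a number instead.

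**2. The plan's own figures**

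Inputs from Analyses: "A sample size of 600 patients, 300 in each arm", "based on sample size calculations for the outcome measure of medication understanding"; 65% rising by 11 points at 80% power; 3 mm Hg with SD 12 at 86%. A two-sided α of 0.05 is assumed, since none is stated.

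Two proportions, with p̄ the average of p₁ and p₂: power = Φ{[|p₂ − p₁|√n − 1.96√(2p̄(1 − p̄))] / √[p₁(1 − p₁) + p₂(1 − p₂)]}.

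- 65% v 76%, n = 300: (0.11 × 17.32 − 1.96 × 0.645) / 0.640 = 1.00, so power is 84.2% (81.8% with continuity correction).
- With 65% read as the average of both arms (59.5% v 70.5%), power is 80.8%.
- Blood pressure: Φ[3 / (12√(2/300)) − 1.96] = Φ(1.10) = 86.5%.

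Both stated figures reproduce, and neither uses regimen consolidation.

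**3. What one fixed cut would cost (illustration only)**

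The article gives no mean, SD or distribution for dosing times, so every input here is assumed. In each case the effect gives about 80% power on the ungrouped measure with 300 per arm. The proportions below each cut then go into the formula in step 2.

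*Normal measure.* Standardised difference = (1.960 + 0.842)√(2/300) = 0.229.

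| Control share below the cut | Intervention share | Power |
|---|---|---|
| 50% | 59.0% | 60% |
| 25% | 32.8% | 56% |
| 10% | 14.6% | 41% |

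*Count A.* Control shares for 1 to 6 times per day: 8, 22, 33, 22, 10, 5%. *Count B.* Control shares for 1 to 5 times per day: 15, 35, 30, 15, 5%. In both, the intervention shifts the underlying normal scale by 0.24 SD. The means become 3.19 v 2.90 (A) and 2.60 v 2.36 (B). Power on the mean is Φ[difference / √((s₁² + s₂²)/300) − 1.96].

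| Analysis | A | B |
|---|---|---|
| Mean count | 81% | 80% |
| Cut at ≤1 | 40% | 52% |
| Cut at ≤2 | 62% | 65% |
| Cut at ≤3 | 62% | 50% |
| Cut at ≤4 | 44% | 25% |
| Cut at ≤5 | 25% | n/a |

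The best fixed cut keeps about 60–65% power; cuts far from the centre keep much less.

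**4. A rule specific to each patient**

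Write the count as the patient's minimum possible dosing times plus the excess. Suppose the intervention acts on the excess alone. Variation in the minimum between patients then adds noise to the raw count but not to a yes/no measure of being at the minimum. With assumed minimum times of 1 to 4, an excess of 0, 1 or 2, and a rise of 11–12 points in patients at their minimum (300 per arm), the binary measure had 77–86% power and the unadjusted count 27–63%. So the direction of the power effect depends on which dichotomy is meant.

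**The case against.** The best defence is that a binary outcome was intended all along: consolidated or not, judged against the fewest dosing times the regimen allows, with the coding left to a fuller document. That reading is plausible, and step 4 shows it could be the better measure, because eligible patients take three or more drugs and differ in how complex their regimens must be. It does not remove the mismatch. The article's definition would still be a count and would need rewriting. This is not detail left out by condensing, because the article states both the definition and the model and they disagree. Nor can the logit be read as a cumulative logit for ordered counts, since the article calls the outcome binary.

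Four stronger readings are tempting, and the documents do not support them:

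- **The plan loses power.** That holds for one fixed cut under assumed distributions, and not for every dichotomy.
- **False positives are inflated.** This would follow only if the cut were chosen after seeing the data. Simulating no true difference (mean 3.0, SD 1, 300 per arm) and taking the best of cuts at ≤2, ≤3 and ≤4 gave p < 0.05 in about 13–14% of trials. Nothing shows that the choice is open, since a plan not shown may fix it.
- **Adherence has the same fault.** Its section names three measures to be triangulated and does not define the outcome as a count. How they are scored and combined is commonly left to a fuller document, so there is no contradiction.
- **The sample size is undermined.** It rests on medication understanding, whose two-way coding is explicit.

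**Conclusion.** The point holds as a contradiction between two sections: the Regimen consolidation section gives a count, the Analyses section treats it as binary, and no rule links them. This rests on the text alone and needs no assumption. The power figures are illustrations with assumed inputs: about 80% falls to 60–65% at the best fixed cut and to as little as 25% at the worst cut examined, with no loss necessarily under a patient-specific rule. The article does not settle which section reflects the intent. The matter should be fixed but does not threaten the trial: one of four key outcomes is affected, the number enrolled and the stated power stand, and the tray data are recorded in enough detail for either analysis.

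**What to change.** Reconcile the two sections before outcome data are analysed.

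- **Default, following the stated definition.** Remove regimen consolidation from the logit list. Model the number of dosing times in PROC GENMOD, with an identity link for a mean difference or a log link with Poisson for a rate ratio. Use robust standard errors. In assumed distribution A the variance is 1.25² = 1.56 against a mean of 3.19, so model-based Poisson standard errors would be too large by a factor of about √(3.19/1.56) = 1.43. Preferably adjust for the baseline number of drugs or minimum possible dosing times, which removes variation that the intervention does not target.
- **If a binary outcome is intended.** Rewrite the definition with the coding rule fixed in advance, for example whether or not the regimen is taken the fewest times per day that it allows. Say how that minimum is derived, keep the logit model, and report the count as supportive.

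Either route changes wording only. It needs no new data, no extra patients and no other software. The article reports enrolment as still under way.
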